#### Trial withdrawal

2.4.4

Patients who require reoperation or chemoradiotherapy due to disease progression, as well as those who withdraw from the study after randomization for any other reason and subsequently cease participation in the intervention or follow−up, will be considered withdrawn from the study. Upon dropout, the investigator is expected to make all reasonable attempts to reach the individual, document the cause of withdrawal, and complete relevant assessments. All data related to the dropout cases should be preserved appropriately for documentation.

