### Randomization, allocation concealment, and blinding

2.6

The randomization schedule for both participants and investigational products was generated using SAS software (version 9.4). Subject randomization and drug allocation will be implemented through the Central Randomization System V5.0 (provided by Beijing Medfuture Technology Co., Ltd.). Eligible patients will be randomized in a 1:1 ratio to receive either the BL-1 group or the placebo group. Simultaneously, the dosage form, properties, odor, appearance, packaging, labeling, and identification of the placebo will be matched with those of the treatment group, and clinical pharmacists prepared the corresponding medications using random numbers to implement allocation concealment for bias minimization (18). All participants and investigating clinicians will remain masked to treatment assignment throughout the trial duration until the final database lock. Designated personnel from the Evidence Based Medicine Centre of West China Hospital will have exclusive access to the randomization list and are mandated to maintain confidentiality until trial completion and full data collection, unless unblinding is necessitated by serious adverse events.

Unblinding of a participant’s assigned intervention will constitute grounds for withdrawal from the study, and the case will be documented accordingly. If 20% or more of the required sample size has their assigned intervention disclosed, the trial can be considered to have failed in maintaining blinding for participants (19). To uphold objectivity and minimize potential bias from investigators and participants, the statistical analysis for this trial will be performed by an independent third party under a blinded manner.

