### Statistical analysis

2.11

Analyses will adhere to the ITT principle, including all randomized patients in their as-randomized groups, provided they received at least one dose of the study intervention (BL-1 or placebo) and completed a minimum of one post-baseline assessment. The PPS and ITT analyses for the primary outcomes will be performed concurrently to verify the consistency of the treatment effects. In cases of discordance between the ITT and PPS, the ITT results will be accorded primacy as the primary analysis for outcome interpretation. The robustness of the trial findings will be substantiated by concordance between the ITT and PPS. The ITT set will be employed for the analysis of baseline characteristics, while the safety set will serve for all safety evaluations. Missing data pertaining to primary outcome measures will be handled through multiple imputation techniques, implemented using R software (version 4.1.2). For remaining categorical variables, no imputation will be performed for missing data, and all available cases will be analyzed as observed.

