
Prompted by the limited treatment options in current guidelines and documented AEs of available therapies, our team undertook a comprehensive investigation into the pathogenesis of LARS through the lens of TCM, while also systematically reviewing the evidence for TCM and acupuncture efficacy and safety (data unpublished). The current evidence regarding LARS treatments is substantially constrained by methodological quality, necessitating rigorously designed investigations to validate TCM’s therapeutic role. Accordingly, we employed a randomized, double-blind, placebo-controlled design to assess the therapeutic potential and safety of the BL-1 prescription in patients with LARS. The key pathogenic mechanism of LARS is that the disease remains in Yangming, and dampness, phlegm and stasis are intertwined. Therefore, this study aims to assess the therapeutic application of BL-1 in managing LARS across a 4-week intervention period. The clinical effectiveness and safety of BL-1 for the treatment of LARS will be evaluated on the basis of the daily frequency of diarrhea, stool consistency, Wexner anal incontinence score, LARSS, LARS response rate, QOL, KPS score, and reduction in the need for acute treatment.

The following limitations should be considered when interpreting the results of this investigation. First, a notable constraint is the absence of validated objective measures for standardized assessment of LARS outcomes. Inter-individual variability and perceptual differences in symptom reporting may introduce substantial variance in documented drug efficacy profiles. Second, treatment dissatisfaction or intolerability of LARS symptoms may adversely affect patient adherence, thereby increasing the dropout rate. Third, as some participants may reside in other provinces, the quality control of the “direct drug delivery to participants” process requires further refinement. To enhance patients’ comprehensive trial awareness, our study staff received specialized training in establishing effective communication channels and building therapeutic rapport.

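### The withdrawal rule does not separate stopping study medication from leaving follow-up, so week-4 primary scores may go uncollected in patients whose dropout is plausibly outcome-related

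*Protocol article*

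**What the plan says.** Section 2.4.4 (Trial withdrawal) puts two groups under the single status of withdrawn from the study:

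- "Patients who require reoperation or chemoradiotherapy due to disease progression";
- patients who, once randomized, withdraw from the study "for any other reason and subsequently cease participation in the intervention" or follow-up.

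Once a patient drops out, the investigator is to "make all reasonable attempts to reach the individual, document the cause of withdrawal, and complete relevant assessments". No time point is attached to those assessments. Section 2.6 adds a further route: "Unblinding of a participant’s assigned intervention will constitute grounds for withdrawal from the study".

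The primary outcome (section 2.7.1) is the change in LARS score from baseline to week 4. Section 2.11 gives the ITT analysis primacy, but restricts that set to randomized patients with at least one dose and at least one post-baseline assessment. On gaps it states: "Missing data pertaining to primary outcome measures will be handled through multiple imputation techniques".

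The Discussion lists as a limitation that "treatment dissatisfaction or intolerability of LARS symptoms may adversely affect patient adherence, thereby increasing the dropout rate".

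**The concern.** An ITT comparison needs the week-4 score of each randomized patient, whether or not the medication was continued. The rule in 2.4.4 does not secure this. Patients who progress are withdrawn by rule, even if they could still answer a questionnaire. For all others, stopping the intervention and stopping follow-up are named as alternatives leading to the same status. A site could reasonably read this as permission to end data collection when medication stops, and two sites could read it differently.

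A score taken at dropout, say on day 10, is not the week-4 outcome. If the week-4 score is not taken, the patient's contribution to the primary analysis is imputed, or the patient leaves the ITT set. The response rate in 2.7.1 is also affected: its denominator is all randomized participants, so these patients count there without an observed week-4 status.

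The article itself links dissatisfaction and intolerable symptoms to dropout, so the gaps need not be random. Section 2.5.1 lists expected effects of BL-1 such as nausea, abdominal pain and bloating, so stopping may also differ between arms. The planned effect is only 1.2 points, and a modest bias is a sizeable part of it.

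**Working it through.** **Inputs, all from section 2.8:** mean reductions of 9.75 (BL-1) and 8.55 (placebo), difference 1.20; SD 2.5; two-sided alpha 0.05; power 0.90; 93 per group evaluable, 117 per group enrolled; withdrawal anticipated below 20%.

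**Step 1: the plan's own figures.** The normal approximation for a difference of 1.20 and SD 2.5 gives 92 per group. The exact t calculation gives 93 (power 0.8994 at 92 and 0.9025 at 93). Allowing for 20% loss, 93 / 0.80 = 116.25, rounded up to 117. Both stated figures reproduce. The allowance is 117 − 93 = 24 per arm, 48 in total, and losing that many still leaves about 90% power. The question is therefore bias, not power.

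**Step 2: what happens to a patient who stops early and is treated as withdrawn.**

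- With a week-2 score, or a score taken at dropout, but none at week 4: in the ITT set, primary outcome imputed.
- With no post-baseline assessment: outside the ITT set, not imputed.
- With a week-4 score: only if the site chose to obtain it, since 2.4.4 does not ask for it at that time.

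**Step 3: bias from imputation.** Let p be the share of an arm without a week-4 score, and g the shortfall, meaning the mean reduction imputed for these patients minus their true mean reduction. Then

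bias in (BL-1 − placebo) = p(BL-1) × g(BL-1) − p(placebo) × g(placebo).

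*Scenario A (assumed).* BL-1 stoppers truly end at the placebo mean but are imputed at the on-treatment mean, so g(BL-1) = 9.75 − 8.55 = 1.20. Placebo stoppers have no shortfall, so g(placebo) = 0.

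- p(BL-1) = 0.10: 0.10 × 1.20 = 0.12 points, 10% of 1.2.
- p(BL-1) = 0.20: 0.20 × 1.20 = 0.24 points, 20% of 1.2.

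Here bias arises even with equal withdrawal shares, because the shortfalls differ.

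*Scenario B (assumed).* The shortfall g is the same in both arms, so bias = g × [p(BL-1) − p(placebo)].

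- Equal shares: 0, whatever g is.
- 20% in BL-1 and 10% in placebo: g = 2.5, 5 and 9 give 0.25, 0.50 and 0.90 points (21%, 42% and 75% of 1.2).
- 10% in BL-1 and 20% in placebo: the same sizes with a negative sign, against BL-1.

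The document gives neither the withdrawal share by arm nor g. These are ranges, not predictions.

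**The case against.** The case on the other side has real force on several points.

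- **The wording puts withdrawal first.** The second group is those who withdraw from the study and then cease. A reader might infer that stopping medication alone counts by rule as leaving the study. The text does not clearly say so; it is ambiguous.
- **Later visits are not cancelled.** The site must make all reasonable attempts at contact and "document the cause of withdrawal, and complete relevant assessments". A reader might infer that week-4 and week-6 scores are forbidden or always lost. The text is only silent on their timing.
- **The patients lost are not simply those who did badly.** The automatic category is limited to disease progression, an oncological event and not LARS non-response. Under 2.5.3, patients with intolerable symptoms or dissatisfaction may take loperamide, which 2.4.4 does not list as withdrawal. The Discussion says only that dropout may increase.
- **The size is set by assumption.** The imputation model is not stated, and a scheduled week-2 score (2.7.2) could inform it. The 20% is a ceiling, and not every withdrawal is a treatment stopper with a missing score. Those who withdraw consent or lose contact cannot be recovered.
- **Scores after progression.** Whether a bowel score after reoperation or chemoradiotherapy still measures the intended outcome is a judgement about the estimand.
- **The source is a condensed article.** Follow-up after stopping may be set out in the full protocol.

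These points limit the strength of the claim but do not remove it. The article does state a withdrawal rule; that rule merges two different events and ties its assessment duty to dropout. An analysis plan can choose how to impute, but it cannot recover week-4 scores that sites were never asked to take.

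**Conclusion.** The point holds in a limited form. Section 2.4.4 does not distinguish stopping study medication from leaving follow-up, and does not require the week-4 LARS score after treatment stops. Such patients may end up imputed or outside the ITT set, and the article's own remark on dropout makes this missingness plausibly outcome-related.

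Under Scenario A the planned difference is inflated by 0.12 to 0.24 points. That assumes 10–20% of BL-1 patients stop, that they truly end at the placebo mean, and that they are imputed at the on-treatment mean. The upper figure uses the withdrawal ceiling. A reader might infer that the bias must favour BL-1, but the document does not support that: it is zero if shares and shortfalls match across arms, and can turn against BL-1 if placebo loses more. Planned power is not in question. The change should be made, because the remedy is inexpensive and works only while data are still being collected.

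**What to change.** In section 2.4.4, define two statuses: discontinued study medication, and withdrew consent to follow-up. State that everyone who still consents, whatever their treatment status, provides the LARS score and the other scheduled patient-reported and adverse-event assessments at weeks 2, 4 and 6, by telephone if needed. In section 2.11, state that these observed scores enter the ITT analysis and that only what is still missing is imputed. For patients with progression-related reoperation or chemoradiotherapy, collecting the score keeps the analysis options open; how it is interpreted can be set out in the analysis plan.

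None of this alters when or why treatment is stopped.

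The cost is a protocol amendment and a few extra telephone questionnaires, for at most about 48 patients on the plan's own allowance. The LARS score has five domains, and regular telephone follow-up is already foreseen in section 2.4.1. With 92 of 234 enrolled at the time of the article (section 2.2), the remaining 234 − 92 = 142 could be covered from entry. The downside is that the estimated effect may be smaller once off-treatment scores are included.

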### Intervention

2.5

#### The experimental group

2.5.1

Participants will be provided with the BL-1 formulation by the West China Clinical Pharmacy Department (Chengdu, China). Some details on BL-1 are listed in **Table 1**. This compound formulation is a water extract of various traditional Chinese medicinal materials: Bupleuri Herba 15g, Ginseng Radix et Rhizoma 15g, Astragali Radix 30g, Atractylodis Macrocephalae Rhizoma 15g, Cimicifugae Rhizoma 15g, Mume Fructus 15g, and Aconiti Lateralis Radix Praeparata 15g (patent number ZL 2024 1 1479878.8). The formulation is supplied at 100ml/bag. Oral supplements were taken three times daily before meals for 4 weeks. The expected adverse effects of BL−1 include nausea, abdominal pain, bloating, constipation, and others.

**Table 1 T1:** Components of BL-1 (patent number ZL 2024 1 1479878.8).

Latin/scientific name	Chinese pinyin	Dose	Sources	Parts or form used
Bupleuri Herba	Chaihu	15g	*Bupleurum marginatum* Wall. ex DC.	Dried
Ginseng Radix et Rhizoma	Rensheng	15g	*Panax ginseng* C. A. Mey.	Dried root
Astragali Radix	Huangqi	30g	*Astragalus membranaceus* (Fisch.) Bge. *var. mongholicus* (Bge.) Hsiao	Dried root
Atractylodis Macrocephalae Rhizoma	Baizhu	15g	*Atractylodes macrocephala* Koidz.	Dried root
Cimicifugae Rhizoma	Shengma	15g	*Cimicifuga foetida* L.	Dried root
Mume Fructus	Wumei	15g	*Prunus mume* (Sieb.) Sieb. et Zucc.	Dried unripe fruit
Aconiti Lateralis Radix Praeparata	Fuzi	15g	*Aconitum carmichaelii* Debx.	Dried root

#### The control group

2.5.2

The placebo, manufactured by the West China Clinical Pharmacy Department (Chengdu, China), will be orally administered at a dose of one bag three times daily before meals over a 4-week course. The placebo is a low-dose mixture prepared using 10% of the therapeutic group’s prescribed dosage. Its appearance and specifications are designed to be indistinguishable from those of the BL-1 formulation. Additionally, post−hoc testing will be performed to verify the validity of blinding. A flow diagram of the trial is shown in **Figure 2**.

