**Methods/design:**

The study will be conducted as a randomized, double-blind, placebo-controlled trial, comprising a 4-week intervention phase and a subsequent 2-week follow-up period. A total of 234 patients with LARS, aged 18 to 75 years, are planned to be enrolled in this study. Eligible participants will be randomized to receive either the BL-1 group or placebo group in a 1:1 ratio. Participants in the experimental group will receive BL-1 formulation, whereas those in the placebo group will receive an indistinguishable BL-1 placebo. The primary outcome measure is the change in LARS score from baseline to week 4. Secondary outcome measures encompass: (a) stool frequency and consistency (assessed via the Bristol Stool Scale); (b) severity of fecal incontinence (evaluated using the Wexner Anal Incontinence Scale); (c) QOL, measured with the European Organization for Research and Treatment of Cancer QOL questionnaire and the Karnofsky Performance Status score; and (d) other patient-reported outcomes. Safety will be monitored continuously throughout the treatment, with assessments including the incidence of adverse events and laboratory abnormalities.

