**Discussion:**

BL-1 is the compound prescription of eleven traditional Chinese medicinal materials: Bupleuri Herba, Ginseng Radix et Rhizoma, Astragali Radix, Atractylodis Macrocephalae Rhizoma, Cimicifugae Rhizoma, Mume Fructus, and Aconiti Lateralis Radix Praeparata (patent number ZL 2024 1 1479878.8). In recent years, BL-1 has been applied to treat digestive system diseases, particularly defecation disorders, and may offer potential benefits for adults with LARS. The absence of robust clinical evidence has prompted the design of this randomized, double-blind, placebo-controlled trial to rigorously evaluate its therapeutic efficacy and safety. This trial is expected to yield critical data that will inform the clinical use of BL-1 formulation in the management of LARS.

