### Study design

2.1

This study is a multicenter, randomized, double-blind, placebo-controlled exploratory trial. The protocol was developed in accordance with the Standard Protocol Items: Recommendations for Interventional Trials guidelines (16). **Figure 1** presents the trial timeline and assessment schedule. Eligible participants will be randomized to receive either the BL-1 formulation or placebo at a 1:1 ratio. The trial for both groups will comprise a 4-week intervention period followed by a 2-week follow-up. Ethical approval was obtained from the Ethics Committee of West China Hospital, Sichuan University (Approval ID: 20241218). The trial was prospectively registered in the Chinese Clinical Trial Registry under the identifier ChiCTR2400087108.

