### Sample size

2.8

On the basis of preliminary results from the pilot trial, the BL-1 treatment group had a score reduction of 9.75 ± 2.30 points, whereas the placebo control group had a reduction of 8.55 ± 2.84 points. The overall mean change in the LARSS was assumed to be 9.75 for the BL-1 group and 8.55 for the placebo group. The variances of the two groups were homogeneous, with a standard deviation of 2.5. A superiority design was adopted, with a two-sided test level set at α = 0.05 and a test power of 1-β = 0.9. A sample size calculation was performed based on a balanced design (1:1 allocation), indicating that 93 participants are required per group. Adjusting for an anticipated withdrawal rate below 20% (24), the target enrollment was planned as 117 patients per group, but the intention−to−treat (ITT) and per−protocol set (PPS) analysis sets will be determined based on the final sample size and completion data at trial end. The data collected in this trial will inform future sample size calculations and provide a foundation for the design of subsequent large-scale clinical trials.

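### The control called a placebo contains BL-1 at 10% of the dosage, so the trial estimates full dose versus one-tenth dose, and its claims and limitations do not say so

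*Protocol article*

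**What the plan says.** Section 2.5.2 (The control group) gives the composition of the comparator: "The placebo is a low-dose mixture prepared using 10% of the therapeutic group’s prescribed dosage". It is "orally administered at a dose of one bag three times daily before meals over a 4-week course", which is the frequency and duration that section 2.5.1 gives for BL-1.

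Elsewhere the label carries no qualification:
- Abstract, Methods/design: "those in the placebo group will receive an indistinguishable BL-1 placebo".
- Abstract, Discussion: a "randomized, double-blind, placebo-controlled trial to rigorously evaluate its therapeutic efficacy and safety".
- Section 2.1: "This study is a multicenter, randomized, double-blind, placebo-controlled exploratory trial".
- Section 2.8: in the pilot, "the BL-1 treatment group had a score reduction of 9.75 ± 2.30 points" while "the placebo control group had a reduction of 8.55 ± 2.84 points". The composition of that pilot control is not given.
- Section 3 (Discussion): "we employed a randomized, double-blind, placebo-controlled design to assess the therapeutic potential and safety of the BL-1 prescription".

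The limitations at the end of section 3 cover the lack of objective measures, adherence and drug delivery. They do not mention that the control contains the study herbs.

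**The concern.** On the natural reading of section 2.5.2, both arms take the same product on the same schedule, one at full strength and one at a tenth. That is a dose comparison, whereas the label promises a comparison with something inert. The article nowhere calls the 10% mixture inactive. Its own rules treat exposure to herbal medicine as able to disturb the assessments: section 2.4.3 excludes recent treatment with traditional Chinese medicine, and section 2.5.4 prohibits other oral herbal medicines during the trial.

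Three readings of the results are at stake:
- **Size of effect.** The estimated difference is not the effect of BL-1 against an inert control.
- **Null result.** A non-significant difference could arise because BL-1 does not work, or because the control works too.
- **Safety.** Safety is a stated aim, with adverse events, liver and kidney function and ECG among the outcomes in section 2.7.2. Similar rates in two arms are usually taken as reassuring. Here both arms are exposed to the same constituents, so similarity would not show that BL-1 adds no harm, and an event in the control arm cannot be presumed unrelated to BL-1.

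**Working it through.** **1. Reproduce the plan's sample size.** Inputs from section 2.8: difference 9.75 − 8.55 = 1.20 points, common SD 2.5, two-sided α = 0.05, power 0.90, 1:1 allocation, withdrawal 20%.

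n per group = 2 × (1.960 + 1.282)² × 2.5² / 1.20² ≈ 91.2, so 92 by the normal approximation. With the two-sample t-test, power is 0.8994 at 92 and 0.9025 at 93, so 93 is required. 93 / 0.80 = 116.25, so 117 per group and 234 in total. The stated figures reproduce, and there is no calculation error.

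**2. The contrast.** The stated ratio is 10 to 1. For a single listed material, for example, 15 g of Aconiti Lateralis Radix Praeparata in Table 1 becomes 1.5 g. A total weight cannot be used: Table 1 lists seven materials, while the abstract speaks of eleven. The ratio does not depend on that count.

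**3. How much of the effect the contrast captures.** No dose-response is given, so every curve here is an assumption. With dose d as a fraction of full dose, share captured = 1 − E(0.1)/E(1). The last column is the effect against an inert control that an observed 1.20 points would then stand for, 1.20 / share.

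| Assumed curve | Share captured | 1.20 / share |
|---|---|---|
| Threshold above 10% | 1.00 | 1.20 |
| Sigmoid Emax, Hill 2, ED50 = 0.5 | 1 − 0.0385/0.800 = 0.95 | 1.26 |
| Linear | 1 − 0.1 = 0.90 | 1.33 |
| Emax, ED50 = 1 | 1 − 0.0909/0.500 = 0.82 | 1.47 |
| Emax, ED50 = 0.5 | 1 − 0.1667/0.6667 = 0.75 | 1.60 |
| Emax, ED50 = 0.1 | 1 − 0.500/0.909 = 0.45 | 2.67 |

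These curves concern efficacy. Toxicity need not follow the same curve, so the table puts no figure on attenuation of adverse event differences.

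**4. Power, which depends on what the pilot control was.** Let f be the assumed share of the full-dose specific effect that the 10% mixture keeps.

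*Case A: the pilot control was inert.* The difference to be expected in this trial is 1.20 × (1 − f). Power at 93 per group is Φ(difference × √(93/2) / 2.5 − 1.96), with the t-test value beside it.

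| f | Difference | Power (normal) | Power (t-test) |
|---|---|---|---|
| 0 | 1.20 | 0.905 | 0.903 |
| 0.1 | 1.08 | 0.838 | 0.834 |
| 0.2 | 0.96 | 0.745 | 0.740 |
| 0.3 | 0.84 | 0.630 | 0.625 |

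*Case B: the pilot control was the same 10% mixture.* The 1.20 points already describe full dose versus 10%, so 93 per group is right for the contrast actually run. The effect against an inert control would be 1.20 / (1 − f): 1.33, 1.50 or 1.71 points for f = 0.1, 0.2 or 0.3. The trial would not estimate it.

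**5. What the pilot can tell.** The pilot control improved by 8.55 / 9.75 = 88% of the improvement with BL-1. That figure mixes natural course, placebo response and any low-dose activity, and the article gives no means of separating them. It is no evidence that the 10% mixture is active or that it is inactive.

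**The case against.** The strongest reply is that the test is one of superiority. Unless response falls with dose, activity in the control only shrinks the difference, so a win over the 10% mixture is conservative evidence that BL-1 works. This stands. A reader might infer that the trial cannot support any efficacy conclusion, and the documents do not bear that out.

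Second, the composition is disclosed in section 2.5.2, the trial is called exploratory, and a justification for 10% may sit in the full protocol, which is not shown. The missing justification is therefore not held against the article. What remains is internal to it: it states the composition and also an unqualified label, and it lists limitations without this one.

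Third, section 2.7.2 already defines adverse event incidence as an absolute proportion, and section 2.11 assigns a safety set. Absolute rates in the full-dose arm stay observable, and only the comparison between arms is weakened. This also stands. The article does not say that similar rates will be read as reassuring. The point is that nothing in it guards against that reading.

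Fourth, a reader might infer that participants, the monitoring board or the ethics committee were not told of the 10% content. The documents do not show this: consent pages were removed, and the ethics and registry files are not at hand.

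**Conclusion.** The point holds as a mismatch between what is compared and what is claimed. The randomized contrast is full-dose versus 10%-dose BL-1. Any activity at 10% biases the efficacy difference and the between-arm safety comparison toward no difference. The effect against an inert control is not estimated, a null result cannot be read as no efficacy, and similar adverse event, laboratory or ECG rates cannot be read as no added harm.

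The size is unknown. Under the assumed curves the contrast keeps from about 45% to nearly 100% of the effect against an inert control, and the low end rests on one chosen curve (Emax with ED50 at a tenth of the full dose). Power is affected only if the pilot control was inert: about 0.84, 0.74 or 0.63 in place of 0.90 for assumed retention of 10%, 20% or 30%. If the pilot used the same mixture, the planned size stands. The conclusion also rests on reading section 2.5.2 as one tenth of the BL-1 materials, which is its plain sense.

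**What to change.** Reconcile the abstract, sections 2.1, 2.5.2 and 2.8, and the discussion:
1. Describe the comparator as a low-dose (10%) BL-1 control, and define the treatment effect as full dose versus 10% dose.
2. State in section 2.8 what the pilot control contained, so that the reader knows which contrast the 1.20 points describe.
3. Add the possible attenuation to the limitations.
4. State before unblinding that a non-significant result will not be taken as evidence of no efficacy, and that the estimate is not an effect against an inert control.
5. State that control-arm events will also be assessed for relation to BL-1, and that safety conclusions will rest on absolute rates in each arm, with similarity between arms not counted as evidence of safety.

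No change to product, dose, sample size or blinding is proposed. The cost is a wording amendment and a registry update, a route that section 2.12 already provides. With 92 of 234 participants enrolled, it can be done well before the data are unblinded. The downside for the sponsor is a less favourable label and a narrower conclusion.
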